## Abstract

**Background:**

In Bangladesh, the targets on reduction of maternal mortality and utilization of related obstetric services provided by skilled health personnel in Millennium Development Goals 5 remains unmet, and the progress in reduction of neonatal mortality lag behind that in the reduction of infant and under-five mortalities, remaining as an essential issue towards the achievement of maternal and neonatal health targets in health related Sustainable Development Goals (SDGs). As access to appropriate perinatal care is crucial to reduce maternal and neonatal deaths, recently several mobile platform-based health programs sponsored by donor countries and Non-Governmental Organizations have targeted to reduce maternal and child mortality. On the other hand, good health-care is necessary for the development. Thus, we designed this implementation research to improve maternal and child health care for targeting SDGs.

**Methods/design:**

This cluster randomized trial will be conducted in Lohagora of Narail District and Dhamrai of Dhaka District. Participants are pregnant women in the respective areas. The total sample size is 3000 where 500 pregnant women will get Mother and Child Handbook (MCH) and messages using mobile phone on health care during pregnancy and antenatal care about one year in each area. The other 500 in each area will get health education using only MCH book. The rest 1000 participants will be controlled; it means 500 in each area. We randomly assigned the intervention and controlled area based on smallest administrative area (Unions) in Bangladesh. The data collection and health education will be provided through trained research officers starting from February 2017 to August 2018. Each health education session is conducting in their house. The study proposal was reviewed and approved by NCCD, Japan and Bangladesh Medical Research Council (BMRC), Bangladesh. The data will be analyzed using STATA and SPSS software.

**Discussion:**

For the improvement of maternal and neonatal care, this community-based intervention using mobile phone and handbook will do great contribution. Thus, a developing country where resources are limited received the highest benefit. Such intervention will guide to design for prevention of other diseases too.

**Trial registration:**

UMIN000025628 Registered June 13, 2016.

## Background

Every year, approximately 290,000 women die due to pregnancy and childbirth, and 99% of maternal mortality occurring in the developing world. Bangladesh is one of those developing countries with high maternal mortality ratio (MMR), standing at 170 per 100,000 live births [1]. Although it has become a lower-middle income country with economic growth and achieved various targets of the Millennium Development Goals (MDGs), the target on reduction of maternal mortality and utilization of related obstetric and reproductive services provided by skilled health personnel remains unmet, and the progress in reduction of neonatal mortality ratio (NMR) lag behind that in the reduction of infant and under-five mortalities, with the proportion of neonatal mortality accounting for 39% of under-five mortality in 1991 increasing up to 60% in 2012 [2]. Reduction of maternal and neonatal mortality therefore remains as a crucial issue for the Sustainable Development Goals (SDGs), which aims to reduce MMR to less than 70 per 100,000 live births and NMR to less than 12 per 1000 live births in all over the world [3].

Accessibility to good-quality health care at both community and referral level is crucial to reduce maternal and neonatal deaths. In rural Bangladesh, where the home delivery by traditional birth attendants accounts for approximately 85% of all child birth [4], antenatal care visits as recommended by the World Health Organization (WHO), childbirth attended by skilled health personnel, and timely referral for emergent maternal and neonatal complications urgently need to be improved. As proved in previous studies, a participatory community-based intervention is effective to improve birth outcomes with low-cost, and realistic to achieve the progress for the rural area [5, 6].

In our proposed community-based intervention, we will test the effectiveness of two essential instruments: mobile phone and home-based maternal records. Mobile phone use is universal in Bangladesh, with the overall coverage of 98% in the population [7]. The costs of text message and audio call are relevantly low. Even in the rural area, where the fixed phones are much less available, mobile phone ownership has widespread and is expected to serve as a potential platform to implement interventions for a continuum of care throughout pregnancy, delivery, and postpartum as highlighted by the WHO [7]. Major effects of a mobile-health program include boosting communications between pregnant women and healthcare providers at different levels, recording their health status for a continuum of care, and providing necessary knowledge, information and guidance to users. It has been increasingly used into various health projects in developing countries [7–12]. A typical home-based health records for mothers and babies, the maternal and child health (MCH) handbook is an effective tool to facilitate client-provider communication and information-sharing, to record health status, to raise health awareness, to identify maternal and neonatal complications, and to encourage health-seeking behaviors [13]. Previous studies in several developing settings indicated its effectiveness to improve health seeking behaviors during pregnancy and postnatal periods [14–18]. On the other hand, its weaknesses are inconvenience to those illiterate, difficulty to preserve the data, and that loss or forgetting to take sometimes occurs. One of the major solution to improve the paper-based MCH handbook, the digitization by an application in a smart phone, an iPad or a desk-top, isn’t realistic in rural Bangladesh, as the coverage of both those electronic tools and the internet are relevantly low. Therefore, we attempt to incorporate the MCH handbook with the mobile short message and audio call, with the rationales that the MCH handbook facilitates the continuum of care throughout pregnancy, delivery and postpartum and has a potential to serve as the essential materials for mobile messages, with a hypothesis that such the intervention will be effective to improve utilization of health care and lead to better maternal and neonatal outcomes. Thus, the objective of the proposed study is to assess the effectiveness to improve birth outcomes and utilization of essential cares in rural Bangladesh, aiming to inform policy making for maternal and neonatal health to achieve the related targets in SDGs.

## Methods

### Study sites and population

This community-based cluster randomized controlled trial (RCT) will be conducted in two Upazilas (sub-districts) in Bangladesh. These two Upazilas are Dhamrai (from Dhaka District in Dhaka division) and Lohagora (from Narail District in Khulna division). Dhamrai has 16 Unions and Lohagora has 12 Unions (the smallest administrative unit in rural Bangladesh). Each Union has 20-25 villages with an approximate population of about 15,000 to 30,000. The rural population in Dhamrai and Lohagora is 306,704 and 215,902, respectively, with an annual birth rate of approximately 20 per 1000 [19]. Although local people supposed to get health care from the Union health care center but the reality is different due to lack of resources. Main source of income in the two study sites is agriculture. And in both areas participants are almost in the same level of education and socio-economically close. There was no related invention or health program during past five years that potentially influence the impact of our proposed study in the two settings. In each Upazila, there is one Upazila health complex and several health and family welfare centers and satellite clinics are located in unions and village level Mobile users are common in the respective areas with a good network by the mobile companies.

Our target population is pregnant women at reproductive age (15-49 years old). Eligible criteria include: 1. currently having a good health status, without any maternal complication, 2. living and planning to give a birth in the study settings during the period from February 01, 2017 to August 30, 2018 and 3. willing to participate to the proposed study with agreement to the informed consent. The study population is an open cohort: those target women will be invited to enter the study when they are detected to be pregnant. Our research team is explaining the procedure of the study and participant’s involvement and if the participants are agreed then received the written consent from the participants of this study. Participants also include community health workers (CHWs), skilled birth attendants (SBAs), staffs from community clinic and support committee for community clinic at the community / primary level. To facilitate referral and consultants from those staffs from the primary level, we will include health professionals working at healthcare facilities of the referral level (Upazilas, districts) to cooperate our intervention. Figure 1 shows the image of our proposed intervention.

**Fig. 1 Fig1:**
[figure not shown]
Study population and intervention

**Fig. 2 Fig2:**
[figure not shown]
Randomization and allocation

### Intervention

In the intervention settings, we plan to fully apply the platform of mobile short messaging and audio system and to effectively link pregnant women and their family members, CHWs and other involved in maternal and perinatal care at the primary level (village and union), and health professionals at the referral level (Upazila and District). Such a network is used to provide information and health education and to boost communication among various stakeholders. The contents of the existing version of Bangladeshi MCH handbook will be incorporated into the mobile platform, with short message or audio message edited based on the gestational age and individual needs. The mobile platform is expected to strengthen the application of MCH handbook. We also are providing books to the participants for each in the intervention areas.

The primary study target is pregnant women. Their families (husbands, mother-in-law and / or mothers) are also invited to participate to the intervention, as they are often the key person to determine daily health-related behaviors, home-based care during and after pregnancy, and seeking and utilization of healthcare services during pregnancy, childbirth and neonatal period in rural Bangladesh. By using the network, pregnant women and their families are possible to daily consult and seek advices during pregnancy with CHWs and to seek basic childbirth and postnatal services to village doctors and SBAs. Meanwhile, it is also possible to realize communications among health care providers at different levels: for example, CHWs, village doctors and SBAs can consult and seek advices and make referral of maternal complications to health professionals at the upper-level facilities (Upazila and District), and health professionals may contact the primary / community-level staffs for the effective referral and provide necessary advices and training as well. As CHWs play an important role to provide primary healthcare to residents in the village community, our trained field staffs will work together with CHWs to take care of pregnant women in intervention group. By integrating CHWs, SBAs and village doctors at the primary level and health professionals at the referral level, the network will also provide advices on a continuum of care to identify complications or any condition needing referral and to alert and help to seeking ANC, SBAs and facility-based healthcare services including emergency care when necessary to pregnant women and their families. As another effective tool to collect data, the MCH handbook will be recorded by CHWs at the primary level, to boost communication between pregnant women and healthcare providers and to implement health education.

This study has been approved by the ethical committee of Bangladesh Medical Research Council, Bangladesh and National Center for Child Health and Development in Japan. We don’t expect the intervention to have adverse effects to the participants and the study sites. The informed content will be implemented targeting all participants, and all paper-based and electronic-based personal information will be anonymous in data analysis.

### Study procedures

The study period includes one-year recruitment of participants and follow-up during pregnancy and the neonatal period. The study starts from February 01, 2017 when we start to enroll the participants, and is expected to finish on August 30, 2018 when all participants go through the neonatal period, four weeks after giving birth. All eligible pregnant women living in the selected villages for the intervention and the control will be recruited right after the allocation. Our trained staffs will visit each household to collect the baseline and the end-of-point data on the pregnancy by using a structured questionnaire at the enrolment and the end of four weeks after delivery or cessation of pregnancy, the ending point of the participation, respectively. In the survey, variables related to the expected outcomes as describe below as well as demographical and socioeconomic characteristics and indicators on knowledge and practices will be obtained. A code to identify each participant during the study period will be created.

In the intervention group, a short message will be sent to the participants to welcome them and the printed version of MCH handbook will be provided to the participants to the intervention. Our trained staffs together with CHWs will build a close linkage with pregnant women and their family members by using mobile short messaging and audio system. To monitor their conditions and make a record, the staffs will send a short message to the participants at the frequency of every two weeks and to alert them to visit for antenatal care in advance, and if necessary, also visit their home to talk with the participants face-to-face. As the coverage of at least four visits of antenatal care recommended by WHO is low in rural Bangladesh, our first target will to improve the number of antenatal care visits. Then, text messages on essential health items including perinatal care, including antenatal care visit, nutrition during pregnancy, intake of iron tablet and folic acid, work, rest and daily activities, husband and families’ support during pregnancy and lactating period, danger signs, list of skilled birth attendants and hospitals, signs of labor, postnatal care, neonatal care, breastfeeding, and family planning, will be edited to be user-friendly and sent accordingly to each participant appropriate to their gestational age and location of the residence. For those cannot read, our staffs will use phone call instead of short messages. For those participants who don’t own a mobile, we will ask the neighbors or the relatives living closely to them to share the mobile where messages could be sent, because of the close liaison in the rural community. Every two month, the enrolled pregnant women and their families and CHWs will be organized to a community meeting by the mobile network, for face-to-face health education, consulting / advices and ANC during pregnancy. Data on health status during pregnancy, childbirth and postpartum, utilization of related healthcare services at community and facility levels, opinions of the participants and maternal and neonatal outcomes will be collected by using the mobile network and home visiting. On the other hand, in the control group, a routine care will be provided usually, but no intervention will be implemented. Related data will be collected by home visiting during the study period and the end-of-point survey.

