### Measurement of outcomes

We don’t expect the intervention to have adverse effects at local and individual level. The primary outcome is neonatal mortality (deaths in the first 28 days per 1000 live-births), Secondary outcomes include maternal mortality (deaths of a pregnant women or within 42 days of cessation of pregnancy from any cause related to the pregnancy or its management, but not from accidental causes), stillbirth, miscarriage (cessation of a presumptive pregnancy before 28 weeks of gestation), preterm birth, low birth weight, maternal morbidities such as pregnancy complications or near miss as an alternative, frequency of antenatal care visits, accessibility to skilled birth attendants for delivery, referral for identified complications, utilization of postpartum care, and status of initiating breastfeeding. We will use International Classification of Diseases version 9 definition of stillbirth for the study settings [20].

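### The eligible birth window and the study both close on August 30, 2018, so births from August 3 to 30 are eligible but cannot be observed for the 28 days that the primary outcome needs

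*Protocol article*

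**What the plan says.** Eligibility (Study sites and population, criterion 2) covers women "living and planning to give a birth in the study settings during the period from February 01, 2017 to August 30, 2018". The cohort is open, and "those target women will be invited to enter the study when they are detected to be pregnant". No minimum gestational age is set.

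On the timetable, Study procedures says: "The study period includes one-year recruitment of participants and follow-up during pregnancy and the neonatal period". Enrolment starts on February 1, 2017, and the study "is expected to finish on August 30, 2018 when all participants go through the neonatal period, four weeks after giving birth". Each woman's closing survey falls at "the end of four weeks after delivery or cessation of pregnancy, the ending point of the participation".

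Measurement of outcomes fixes the horizon: "The primary outcome is neonatal mortality (deaths in the first 28 days per 1000 live-births". The Abstract also places data collection between February 2017 and August 2018, so the article describes no later field work.

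**The concern.** The last permitted birth and the end of the study fall on the same day, yet every participant is supposed to be four weeks past birth by then. Both cannot be true for a woman who delivers in the last four weeks of the window.

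What is at stake is follow-up that depends on length of gestation. Of two women with the same due date in August 2018, the one who delivers early can be followed for 28 days and the one who delivers at term cannot. If incompletely followed births are dropped, preterm births are over-represented among the late enrolees who remain. If they are kept in the denominator, deaths after closure are missed. Either way neonatal mortality is affected, and dropping them also shifts the preterm and low-birth-weight proportions. The 25% loss to follow-up in Statistical analysis does not deal with this: it enlarges the sample, whereas this loss is related to the outcome.

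**Working it through.** **Step 1. The two dates, from the document alone.** Inputs: window and study close on August 30, 2018; follow-up after birth is 28 days.
- Last birth that can be followed: August 30 − 28 days = August 2, 2018.
- End of follow-up for the last eligible birth: August 30 + 28 days = September 27, 2018.

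The stated finish date therefore cannot be reproduced from the stated birth window. Births from August 3 to 30 (28 days) are eligible but not fully observable.

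**Step 2. Recruitment.** The closing date is not stated; one year from February 1, 2017 gives January 31, 2018.
- January 31 to August 30, 2018 = 211 days.
- 211 − 28 = 183 days = 26.1 weeks available before birth.
- Gestational age needed on the last recruitment day, for delivery at 40 weeks: 40 − 26.1 = 13.9 weeks. For delivery at 37 or 42 weeks it is 10.9 or 15.9.

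**Step 3. How many enrolment days are truncated.** Gestational age at enrolment, *g* weeks, is an assumption. Delivery is taken at 40 weeks.
- A = last enrolment date that allows completion = August 2, 2018 − 7 × (40 − *g*) days.
- B = last enrolment date still eligible = the earlier of January 31, 2018 and August 30, 2018 − 7 × (40 − *g*) days.
- Truncated days = B − A, or 0 if negative.
- Share of a uniform year = truncated days / 365.
- Share if women already pregnant at the start are added = truncated days / (365 + 7 × (40 − *g*)).

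| *g* (weeks) | A | B | Truncated days | Share of year | Share with women already pregnant |
|---|---|---|---|---|---|
| 4 | Nov 23, 2017 | Dec 21, 2017 | 28 | 7.7% | 28/617 = 4.5% |
| 6 | Dec 7, 2017 | Jan 4, 2018 | 28 | 7.7% | 28/603 = 4.6% |
| 8 | Dec 21, 2017 | Jan 18, 2018 | 28 | 7.7% | 28/589 = 4.8% |
| 10 | Jan 4, 2018 | Jan 31, 2018 | 27 | 7.4% | 27/575 = 4.7% |
| 12 | Jan 18, 2018 | Jan 31, 2018 | 13 | 3.6% | 13/561 = 2.3% |
| 14 | Feb 1, 2018 | Jan 31, 2018 | 0 | 0% | 0% |

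The cap is 28 days because criterion 2 excludes women due after August 30. If the target of 3000 were enrolled evenly over the year, 28/365 × 3000 is about 230 women.

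**Step 4. Selection on gestation.** A woman enrolled on January 31, 2018 at 10 weeks is due on August 29 and is eligible. She completes only if she delivers by 10 + 26.1 = 36.1 weeks. At 12 weeks the limit is 38.1 weeks.

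**The case against.** **The recruitment part is conditional.** A reader might infer that a year of recruitment simply cannot be followed by August 30, 2018. The document does not support that: gestational age at detection is not given, and from about 14 weeks nobody is lost. This stands.

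**Larger shares would be wrong.** Counting every enrolment day after A gives 41 days (11.2% of a year) at 8 weeks and 55 days (15.1%) at 6 weeks. But 13 and 27 of those days belong to women due after August 30, whom criterion 2 already excludes.

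**Intake may be front-loaded.** Study procedures also says that all eligible women are recruited straight after allocation, and Randomization and masking starts from full lists of pregnant women. Six average Unions per Upazila give (306,704/16 + 215,902/12) × 6 × 0.020, about 4,460 births a year. At full uptake, new pregnancies alone would reach 3000 in 3000/4,460 × 365, about 246 days, which is early October 2017. The late group could then be small or absent. Uptake is not stated, however, and a one-off intake would contradict the one-year recruitment and the open cohort. The conflict between the written dates remains in any case.

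**The finish date is only expected.** No rule says that data stop on August 30 or that only completers are analysed, and an article may leave closure handling to the full protocol. That is fair. Still, both dates are stated here, and they disagree.

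**Arm bias.** A reader might infer a biased comparison. The cut-off is common to all arms, and women are listed from the same source in all selected Unions. Nothing in the document shows that detection is earlier in one arm.

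**A 42-day cut-off.** Maternal mortality runs to 42 days, but participation ends at four weeks and no 42-day visit exists. That is a separate matter.

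**Conclusion.** The date conflict is certain and needs no outside assumption: births from August 3 to 30, 2018 are eligible but cannot reach 28 days by the stated finish, and full follow-up of the window needs September 27.

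The number of women affected is modest and depends on an unstated gestational age. Under a 40-week delivery, a fixed age at enrolment and uniform one-year intake, it is 0% from 14 weeks, 3.6% at 12 weeks, 7.4% at 10 weeks and at most 7.7% at 8 weeks or earlier. It falls to between 2.3% and 4.8% for ages of 4 to 12 weeks if women already pregnant at the start are counted.

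The main effect is on absolute neonatal mortality and on the preterm and low-birth-weight mix. Bias between arms would arise only if timing of detection differed by arm. The primary outcome is affected and the correction is simple, so the dates should be reconciled.

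**What to change.** Reconcile the two dates in one of two ways:

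1. Limit criterion 2 to an expected delivery date no later than August 2, 2018, applied identically in all Unions. Recruitment then closes slightly earlier for early pregnancies.
2. Keep the birth window and state that follow-up continues until the last participant's four-week visit, to about September 27, 2018. This costs about four more weeks of existing field work.

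If closure stays at August 30, define the analysis set by expected rather than actual delivery date, so that early births are not selected. The Discussion notes that gestational age is self-reported without ultrasound. The expected date is therefore imprecise relative to a four-week problem, and the text should say so.
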